##### Data management and analysis

###### Curation

A statistician, with support from a data manager, will complete data quality checks on the data extract, identifying missing and incongruent values.

###### Describing sample and patient outcomes

The characteristics of the calls for suspected seizures (dispatch codes, time of day, day of week, location), the patients accounting for them and the ambulance response they receive (proportions managed by ‘Hear & Treat’, ‘See & Treat’, ‘See & Convey to ED’ and ‘See & Convey elsewhere’) will be described.

For events receiving the response ‘See & Convey to ED’, we shall:

Tabulate ED discharge diagnoses.Calculate the proportion satisfying the AA definition.Tabulate the reason/s why persons did not satisfy the AA definition.Calculate the proportion recontacting the UEC system within 3 (and 30) days (with and without inclusion of those whose subsequent contact/s meet the AA definition).Calculate the proportion dying within 3 (and 30) days and reasons.

For events receiving a face-to-face response but not conveyed to ED (ie, ‘See & Treat’, ‘See & Convey elsewhere’), we shall:

Calculate the proportion recontacting UEC system within 3 (and 30) days (with and without those whose subsequent contact/s meet the AA definition; also, with and without those originally non-conveyed to ED because they refused).^14 73^
Calculate the proportion dying within 3 (and 30) days and reasons.

###### Derivation of prediction models and management of missing data

As the outcome measures are binary, multivariable logistic regression will be used to derive the predictive models.^57^ Reporting will be done according to best practice.^74^ The pool of candidate predictors for testing will be informed by WP1b (see WP1b: KE workshops) and chosen based on clinical relevance, consistency in measurement and ease of use in practice.^75^ Where possible, variables will be used in their original form.

While missingness on core data items is anticipated to be low,^62 76^ missingness on wider items might be higher since tests may not be performed if expected to be normal and not all PCR fields are mandatory.^77 78^ Where data are ‘expectedly’ missing (ie, the test is not performed as not clinically indicated), an additional category of ‘not clinically indicated’ will be added to the variable. In the case of more than 10% missingness for any other variable, multiple imputation via chained equations will be undertaken. A set of 20 imputed data sets will be created using predictive mean matching.^79^ Functional form for continuous variables will be assessed via fractional polynomials within each imputed data set.^80^ Variables will be selected for inclusion in the final model within each imputed data set via backward selection with a p value of 0.10. Variables that feature in at least 10 of the 20 imputed models will be selected for the final model. Pooled OR and intercepts will be calculated according to Rubin’s rule.

Apparent measures of model performance will be calculated for the final multiple imputed model. The area under the receiver operating characteristic curve will be calculated to assess the final model’s discriminative performance. Discrimination refers to the ability of the prognostic model to differentiate between those who experienced the event and those who did not. We will report the calibration slope and the ratio of expected to observed events to evaluate calibration, how closely the probability of the event predicted by the model agrees with the observed probability. C-statistics resulting from the imputed data set will be pooled via robust methods and therefore the median of the imputed estimates will be presented.^81 82^ Calibration will also be observed via a calibration plot for each imputed data set separately and the median of the imputed estimates provided.^82^

To account for sampling variability and enable adjustment of the regression coefficients for overfitting,^83^ the final model will be internally validated via bootstrap resampling. In each of 500 bootstrap samples, the entire modelling process, including predictor selection, will be repeated and the apparent model performance (calibration and discrimination in the bootstrap sample) will be compared with the performance in the original sample per multiple imputed data set. The median optimism across all imputed samples will then be used to calculate the optimism-adjusted C-statistic and optimism-adjusted calibration slope.^84^ Using the latter as a uniform shrinkage factor, all the predictor effects in the final developed model will be penalised in order to account for overfitting.^85^

The pool of potential predictors for the backward selection will be any predictor in a final multivariable model for each imputed data set.

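### Fractional polynomial form is chosen separately in each of 20 imputed data sets, with no rule for a common form before pooling by Rubin's rule

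*Protocol article*

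**What the plan says.** Everything here stands in the Protocol article, WP1a, *Derivation of prediction models and management of missing data*.

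- Default form of predictors: "Where possible, variables will be used in their original form".
- Tests left out because they were not indicated: "an additional category of ‘not clinically indicated’ will be added to the variable".
- When other missing data are imputed: "In the case of more than 10% missingness for any other variable, multiple imputation via chained equations will be undertaken".
- Number of imputations and imputation method: "A set of 20 imputed data sets will be created using predictive mean matching".
- Shape of continuous predictors: "Functional form for continuous variables will be assessed via fractional polynomials within each imputed data set".
- Selection inside a single data set: "Variables will be selected for inclusion in the final model within each imputed data set via backward selection with a p value of 0.10".
- How the 20 selections are combined: "Variables that feature in at least 10 of the 20 imputed models will be selected for the final model".
- Pooling of the estimates: "Pooled OR and intercepts will be calculated according to Rubin’s rule".

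The text on internal validation then repeats the whole modelling process in 500 bootstrap samples and shrinks the coefficients by the optimism-adjusted calibration slope. Those coefficients go into the Excel-based draft tool and, under WP2, are applied to the later cohort for temporal validation.

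**The concern.** Rubin's rule averages estimates of the same quantity across imputed data sets. A fractional polynomial coefficient belongs to a particular transformation of the predictor. If one data set selects the logarithm and another the square, their two coefficients multiply different terms, and their average estimates nothing.

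The plan foresees that the data sets may disagree on which variables to include and settles this with the 10-of-20 vote. It has no matching step for shape. The stated sequence therefore runs cleanly only when the 20 data sets happen to agree on the powers. They are least likely to agree when a predictor is clearly non-linear and has many imputed values, and clear non-linearity is the reason for using fractional polynomials at all.

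The pooled coefficients become the risk estimates in the tool. An unwritten choice made at the analysis stage would also be hard to repeat in 500 bootstrap samples. If it is not repeated there, the optimism correction misses it.

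A secondary matter is coding. The article does not say how an added category is combined with a continuous measurement, or how fractional polynomials apply to such a variable.

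**Working it through.** **The plan's own figures.** No stated number is in dispute. The *Sample size* section gives 2194 index events for models (2) and (3) with 40 candidate parameters. The shrinkage criterion of the sample-size formulae it cites, with shrinkage S = 0.9 and an assumed Cox–Snell R² of 0.15 (not stated in the article, but it reproduces the figure), gives

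n = 40 / [(0.9 − 1) × ln(1 − 0.15/0.9)] = 2193.9, rounded up to 2194.

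This figure is used as the sample size in the simulation below.

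**Why differing powers do not pool.** Scale x so that its mean is 1. For a one-term form b·x^p the slope at the mean is p·b. If the data sets agree on that slope, s, the coefficient is b = s/p:

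- p = −2: b = −s/2
- p = −1: b = −s
- p = 1: b = s

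One replicate of the simulation (log effect, 30% missing) chose p = −2 in 18 data sets, p = −1 in one and p = 1 in one. The plain average is

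[18 × (−s/2) + (−s) + s] / 20 = −9s/20 = −0.45s.

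Attached to x^−2, this gives a slope of (−2) × (−0.45s) = 0.9s. Attached to x, it gives −0.45s, which has the wrong sign. So when nearly all data sets agree, the harm is small provided the majority form is kept, but the plan does not say that it is.

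**How often the powers differ (illustration under assumptions).** The set-up was:

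- one positive, skewed predictor and one covariate, n = 2194, about 12% to 14% events;
- 15% or 30% of the predictor missing completely at random;
- 20 imputations by predictive mean matching;
- fractional polynomials of up to two terms, chosen by a closed test at 0.05, with 0.10 for inclusion;
- 10 replicates per setting.

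| True effect | Missing | Replicates with all 20 in agreement | Mean share of the most frequent form | Most distinct forms in a replicate |
|---|---|---|---|---|
| Linear | 15% | 8 of 10 | 0.98 | 2 |
| Linear | 30% | 7 of 10 | 0.93 | 2 |
| Log | 15% | 7 of 10 | 0.97 | 2 |
| Log | 30% | 6 of 10 | 0.90 | 3 |
| U-shaped | 15% | 1 of 10 | 0.49 | 9 |
| U-shaped | 30% | 0 of 10 | 0.48 | 10 |

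Two cautions apply. Ten replicates give only a rough proportion. A data set that drops the variable counts as a different form here; in one linear replicate the split was 18 linear and 2 dropped, which the 10-of-20 vote already resolves. The linear and log rows may therefore understate agreement on powers.

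For the U-shaped effect the most frequent form held on average 0.48 × 20 = 9.6 or 0.49 × 20 = 9.8 data sets, just under 10. Extending the existing vote to powers would thus often leave no winner.

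**Coding of the added category.** A logistic model with a 0/1 not-measured indicator and the continuous value (set to zero where not measured) was fitted to simulated data with n = 2194 and 40% not measured. It gave a slope of 0.356 (standard error 0.063) against a true value of 0.3. The category can be added and the predictor kept continuous.

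**The case against.** The article does not say that coefficients on different powers will be averaged. It says that form is assessed in each data set and then speaks of one final model. Settling on a common form, refitting and pooling is compatible with that wording, and an analysis plan that is not shown may say so. Missing data may also be slight: Table 3 reports under 2% missing for most core clinical variables in earlier work, and imputation starts only above 10%. With little imputation, or with linear effects, the data sets will mostly agree. All of this stands, and it limits the size of the point. It does not remove it, because the article itself fixes the level at which form is chosen, the vote and its threshold, and the pooling rule. As written, that sequence is complete for inclusion and incomplete for shape.

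Three stronger readings are tempting, and the document supports none of them.

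- A reader might infer that the added category forces continuous predictors into bands and so contradicts the original-form rule. The text mentions no bands or cut-points, an indicator beside the continuous value satisfies the sentence, and the original-form rule applies only where possible.
- A reader might then attach a loss of information to that banding, for instance from a median split. The plan proposes no split, so no such loss can be charged to it.
- A reader might infer that fractional polynomials chosen per data set can never be pooled. They can whenever the powers coincide.

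**Conclusion.** The point holds in a limited form. Choosing the form within each imputed data set and then applying Rubin's rule is valid only when all 20 data sets share the same powers, and the plan has no step that ensures this. The breakdown is most likely for clearly non-linear predictors with substantial imputation. In the simulation, full agreement occurred in 1 of 20 replicates with a U-shaped effect (1 + 0 over the two settings) and in 28 of 40 with a linear or log effect (8 + 7 + 7 + 6). These figures rest on one predictor, assumed effect shapes and assumed missingness; the article does not say which continuous predictors will be imputed or how far they depart from linearity. If none exceeds 10% missing, the problem may not arise.

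The coding of the added category is a clarification and not an error. Overall this is a low-priority improvement: a better method than the stated one is available at almost no cost.

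**What to change.** 1. Replace the choice of form within each imputed data set by one common form per continuous variable, chosen across the imputations. Either the likelihood summed over the 20 stacked data sets with weights 1/20 or pooled Wald statistics would serve.
2. Hold that form fixed in all 20 data sets, then run the backward selection, the 10-of-20 rule and Rubin pooling as planned.
3. Repeat the same step inside each of the 500 bootstrap samples. Each resample should draw the same patients in all 20 data sets, so that a common form can be chosen there too.
4. State that, for a continuous test not performed, the added category is a 0/1 indicator beside the measured value, with the value term set to zero where the test was not done. Fractional polynomials then apply to the measured values only.

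The cost is a few sentences and minor code, plus one extra candidate parameter per affected variable. That parameter, like any additional fractional polynomial terms, counts towards the 40 used in the sample-size calculation.

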### Routine data source: cured+

For WP1a and WP2, we will use a cutting-edge database called ‘CUREd+’. Currently being developed by the Centre for Urgent and Emergency Care Research,^64^ it will map UEC use by individuals served by the Yorkshire Ambulance Service (YAS) from 2011 to 2022. It contains records of all ambulance contacts and these are linkable to any subsequent ambulance, hospital (ED, inpatient) and death records (Office for National Statistics (ONS) mortality register). Further information is provided in table 3.

**Table 3 T3:** Key information about CUREd+ linked database

Issue	Detail
Linkage	CUREd+ is a prelinked data set. Events have been linked by NHS Digital using their algorithm based on NHS number, date of birth, postcode and sex.
Coverage of data	CUREd+ is new. Evidence from its predecessor CUREd (which mapped activity in the same area from 2011 to 2017 using a different approach^122^) indicates CUREd+ should have high data coverage. Evidence from CUREd and other work shows ~85% of individuals can have their ambulance and onward care records linked and so are suitable for inclusion.^104 123 124^ Wider work also shows those who can and cannot have their records linked do not markedly differ.^22^ CUREd+ could have even higher coverage due to more use of NHS numbers by ambulance services^125^ (which supports linkage).
Quality of data	The data contributing to CUREd were high in quality.^121 125 126^ Smyth^76^ examined ambulance patient care records (PCRs) for >22 000 patients. Most core clinical variables had <2% missing data and errors were rare. CUREd+ could have even higher quality due to the introduction of electronic PCRs (which support more consistent data capture).
Area covered by CUREd+ and suitability for RADOSS	England has 10 regional ambulance services. CUREd+ includes data from the Yorkshire Ambulance Service (YAS). The size of the population (~5.6 million) and geographical area (urban/rural mix, ~6000 square miles) served by YAS is similar to the average, as is its non-conveyance rate.^33^

NHS, National Health Service; RADOSS, Risk of Adverse Outcomes after a Suspected Seizure.

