##### Sample size

Predictive models for the (1) risk of death/UEC recontact following conveyance, (2) risk of death/UEC recontact following non-conveyance, and (3) risk of an AA following conveyance could be developed. To permit robust testing of at least 40 candidate predictor parameters for each of these models, Riley *et al*’s^72^ formulae using standard parameters indicate: for model (1), a need for 2567 index events, with 103 experiencing the target event; for model (2), a need for 2194 index events, with 308 experiencing the target event; and for model (3), up to 2194 index events, with 461 experiencing the target event. Twelve months of YAS data should be sufficient to satisfy these requirements. Online supplemental file 3 details the reasons why and provides further information on the sample size calculation.

10.1136/bmjopen-2022-069156.supp3Supplementary data

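### The trigger for multiple imputation looks at one variable at a time (more than 10% missing) and leaves handling at or below 10% undefined; if the default is complete cases, losses accumulate across the candidate pool

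*Protocol article*

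**What the plan says.** The rules are in the WP1a section on derivation of prediction models and management of missing data. They treat two kinds of gap differently.

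- Where a test was not done because it was not needed, "an additional category of ‘not clinically indicated’ will be added to the variable". Such records stay in the analysis.
- For everything else: "In the case of more than 10% missingness for any other variable, multiple imputation via chained equations will be undertaken". Then: "A set of 20 imputed data sets will be created using predictive mean matching".

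Variables at or below 10% are not mentioned, and neither is complete-case analysis. The text also does not say whether one variable above 10% leads to imputation of that variable alone or of all incomplete variables. Variable selection, pooling and bootstrap validation are then described as if 20 imputed data sets always exist.

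On how much missingness to expect, Table 3 reports for earlier ambulance records: "Most core clinical variables had <2% missing data and errors were rare". The derivation section adds that "missingness on wider items might be higher since tests may not be performed if expected to be normal" and that some record fields are not mandatory, but gives no figure.

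The WP1a Sample size section sets the size of the predictor pool: "To permit robust testing of at least 40 candidate predictor parameters for each of these models".

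**The concern.** The threshold looks at each variable separately, but a multivariable logistic model needs a record to be complete on every predictor entered. Backward selection starts from the whole candidate pool, so the relevant quantity is the share of records with at least one gap. No single variable's percentage shows that share. A data set can have every variable below 10% missing and still have few complete records.

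At stake are events and precision, against sample sizes worked out for complete data. If completeness is related to outcome, the coefficients and intercept can also be biased. The model for death or recontact after non-conveyance supplies the tool's estimate of the risk of leaving a patient at home, and it is drawn from the smaller cohort, since about 70% of cases are conveyed (Table 2).

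**Working it through.** **The plan's own sample sizes.** The article says only that standard parameters were used. With 40 parameters, target shrinkage 0.9 and a Cox-Snell R² of 0.15 (my assumption, back-solved from 2194), the stated sizes reproduce:

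- Shrinkage criterion: n = 40 / [(0.9 − 1) × ln(1 − 0.15/0.9)] = 2193.9, so 2194. This governs models 2 and 3. Events: 2194 × 0.14 = 307.2 (308 stated) and 2194 × 0.21 = 460.7 (461 stated).
- Model 1, event rate 4%: the criterion limiting optimism in Nagelkerke R² to 0.05 governs and gives 2566.9, so 2567. Events: 2567 × 0.04 = 102.7 (103 stated).

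These agree with the article's Sample size section, which gives, for example: "for model (2), a need for 2194 index events, with 308 experiencing the target event". As reproduced, they contain no allowance for records lost to missing predictors.

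**Complete-case retention.** Let k be the number of incomplete variables and q the share missing on each.

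- Independent gaps: retained = (1 − q)^k
- Non-overlapping gaps: retained = max(0, 1 − kq)
- Fully nested gaps: retained = 1 − q

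The article gives no per-variable figure other than the under-2% statement, so q and k are assumptions shown over a range.

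| k | q | Lost, independent | Lost, non-overlapping | Lost, nested |
|---|---|---|---|---|
| 10 | 2% | 18% | 20% | 2% |
| 10 | 5% | 40% | 50% | 5% |
| 20 | 2% | 1 − 0.98^20 = 33% | 40% | 2% |
| 20 | 5% | 1 − 0.95^20 = 64% | 100% | 5% |
| 20 | 9% | 1 − 0.91^20 = 85% | 100% | 9% |
| 40 | 1% | 1 − 0.99^40 = 33% | 40% | 1% |
| 40 | 2% | 1 − 0.98^40 = 55% | 80% | 2% |

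None of these rows reaches the 10% trigger. With independent gaps, half the records go at 6.7% each on 10 variables, 3.4% on 20 or 1.7% on 40. A mixed case of 30 variables at 0.5% and 10 at 5% keeps 0.995^30 × 0.95^10 = 51.5%.

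**The two readings of the trigger.**

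- One variable above 10% leads to imputation of all incomplete variables: no record is lost once the trigger fires. If no variable exceeds 10%, nothing is imputed, the table applies, and the later steps built on 20 imputed data sets have no defined form.
- Only the variable above 10% is imputed: the table applies to the remaining incomplete variables whether or not the trigger fires.

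**The case against.** The strongest reply is that complete-case analysis is nowhere stated. The article is a condensed account, the later steps assume imputed data, and chained equations normally fill every incomplete variable in the model. The investigators expect higher missingness on wider items, so they probably expect the trigger to fire. That stands as a limit on the claim: dropping records is the software default where the text is silent, not a declared method. It does not rescue the threshold, which the article does fix and which ignores the cumulative share of incomplete records on either reading.

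Several stronger inferences are tempting and should not be drawn.

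- *That most records will be lost.* The pool is counted in parameters. Categories and polynomial terms each use some, so there may be well under 40 variables, and dispatch and demographic fields may be nearly complete. Gaps clustered in the same records lose far less.
- *That independence is the worst case.* Non-overlapping gaps are worse, as the table shows.
- *That skipped tests are left unhandled.* The extra category keeps those records. Only other gaps, such as unfilled non-mandatory fields, fall under the 10% rule. Nothing in the article shows that complete records belong to sicker patients.
- *That model 2 will fall short of its requirement.* The article's figures give about 211 000/10 × 0.90 × 0.85 × 0.30 = 4842 non-conveyed incidents, and 4842 × 0.98^40 = 2158 against 2194 needed. The shortfall is 36 records. It disappears with 39 variables at 2% (2202) or 40 at 1.9% (2248). The 4842 also counts incidents while the unit of analysis is the patient, so repeat callers would lower it. The comparison shows limited room, not a demonstrated deficit.

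**Conclusion.** The point holds as a badly chosen and incomplete rule. The threshold is set per variable, handling at or below it is undefined, and the default would discard records cumulatively. It arises in every case if only the variable above 10% is imputed, and only when none exceeds 10% if the trigger covers the whole data set.

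The loss cannot be fixed at one figure. It depends on how many candidates are incomplete, how incomplete they are and how far the gaps overlap, none of which the article gives. Nested gaps cap the loss at 10%, while independent gaps on 20 variables at 2% to 5% would cost a third to nearly two thirds of records. Bias is a possibility that depends on whether completeness relates to outcome; the article does not settle this. The change is worth making before the models are derived, because the better method uses machinery already planned.

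**What to change.** Remove the 10% threshold and state instead:

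- Tests missing because they were not indicated keep their separate category.
- Every other candidate predictor with any missing value is imputed by chained equations, whatever its percentage missing.
- Imputation is run separately for the conveyed and non-conveyed cohorts. Each imputation model contains all candidate predictors and the outcome or outcomes modelled in that cohort: death or recontact in both, and avoidable attendance in the conveyed cohort only, where it is defined.
- A complete-case analysis is reported as a sensitivity analysis, with the number of complete records and events for each model.

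The 20 data sets, the selection rule, pooling and bootstrap can stay as written, and they would then have a defined input whenever any such predictor value is missing. The cost is a rewritten sentence or two, a slightly larger imputation model in each cohort, and more computing time.

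### The bootstrap is said to repeat the whole modelling process, yet its backward selection starts from predictors already selected; this gives less estimated optimism and less shrinkage than the promised process

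*Protocol article*

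**What the plan says.** All of this stands in the Protocol article, WP1a, under Derivation of prediction models and management of missing data.

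- Candidates at derivation: "The pool of candidate predictors for testing will be informed by WP1b". The Sample size section plans for at least 40 candidate parameters per model.
- Selection at derivation: "Variables will be selected for inclusion in the final model within each imputed data set via backward selection with a p value of 0.10". A variable enters the final model if it is kept in at least 10 of the 20 imputed data sets.
- Internal validation: "In each of 500 bootstrap samples, the entire modelling process, including predictor selection, will be repeated".
- Use of the result: "The median optimism across all imputed samples will then be used to calculate the optimism-adjusted C-statistic and optimism-adjusted calibration slope". That slope is the uniform shrinkage factor, by which "all the predictor effects in the final developed model will be penalised".
- Closing sentence, in a paragraph of its own: "The pool of potential predictors for the backward selection will be any predictor in a final multivariable model for each imputed data set".

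The shrunken models form the draft tool, and WP2 tests them under Temporal validation of predictive models.

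**The concern.** A bootstrap measures selection optimism only if it repeats the selection. Screening 40 or more parameters at p = 0.10 keeps some noise variables and favours true predictors whose effects are overestimated by chance. If each bootstrap sample starts from the survivors of that screen, this part of the optimism is largely unseen. The adjusted C-statistic and calibration slope then look better than under the full process, and the coefficients of all three models are shrunk less. Under-shrunk models give predicted risks that are too extreme at both ends. The two statements also give different published coefficients, so the choice between them should not be left until results are known.

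**Working it through.** **1. Which selection the closing sentence describes.** At derivation the pool is the candidate list, and the final model in each imputed data set is the output of backward selection from it. A pool made of those outputs cannot be the input to the same step. The sentence can only govern the re-selection in the bootstrap, where it conflicts with the statement that "the entire modelling process, including predictor selection, will be repeated".

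**2. The plan's own figures.** The article states no optimism or shrinkage figure, but its sample sizes fix a setting. With P = 40 and an inferred Cox-Snell R² of 0.15 (the inputs are in a supplement not shown):
- Criterion 1, S = 0.9: n = P / [(S − 1) ln(1 − R²/S)] = 40 / (0.1 × 0.1823) = 2194. This matches models 2 and 3.
- Criterion 2, model 1: risk 103/2567 = 0.04 and maximum R² = 0.2853, so S = 0.15 / (0.15 + 0.05 × 0.2853) = 0.9132. Then n = 40 / (0.0868 × 0.1794) = 2567. This matches.

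**3. Single data set at those sizes.** Optimism is the mean over bootstraps of C in the bootstrap sample minus C of the same model in the original data. The shrinkage factor is the mean slope of the bootstrap models in the original data. Design: 40 independent normal candidates, backward selection at p = 0.10, 60 replicates × 60 bootstraps, truth taken from 40,000 new patients. Entries are true / full pool / restricted pool.

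| Model (N, risk) | R² | True predictors | C optimism | Slope |
|---|---|---|---|---|
| 1 (2567, 4%) | 0.15 | 8 | 0.009 / 0.014 / 0.005 | 0.895 / 0.833 / 0.937 |
| 1 | 0.15 | 40 weak | 0.022 / 0.018 / 0.014 | 0.777 / 0.777 / 0.820 |
| 1 | 0.03 | 8 | 0.051 / 0.058 / 0.022 | 0.769 / 0.750 / 0.902 |
| 1 | 0.03 | 40 weak | 0.092 / 0.069 / 0.039 | 0.596 / 0.709 / 0.826 |
| 2 (2194, 14%) | 0.15 | 8 | 0.016 / 0.020 / 0.007 | 0.918 / 0.898 / 0.962 |
| 2 | 0.15 | 40 weak | 0.029 / 0.027 / 0.021 | 0.861 / 0.866 / 0.893 |
| 2 | 0.05 | 8 | 0.027 / 0.037 / 0.013 | 0.844 / 0.805 / 0.927 |
| 2 | 0.05 | 40 weak | 0.053 / 0.046 / 0.028 | 0.703 / 0.756 / 0.840 |
| 3 (2194, 21%) | 0.15 | 8 | 0.013 / 0.019 / 0.007 | 0.929 / 0.905 / 0.966 |
| 3 | 0.15 | 40 weak | 0.027 / 0.025 / 0.020 | 0.867 / 0.876 / 0.900 |
| 3 | 0.05 | 8 | 0.023 / 0.033 / 0.011 | 0.847 / 0.804 / 0.928 |
| 3 | 0.05 | 40 weak | 0.046 / 0.041 / 0.025 | 0.705 / 0.759 / 0.840 |

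In all 12 rows the restricted pool shows less optimism than both the full pool and the truth. The slope gap between pools runs from 0.024 (0.900 − 0.876) to 0.152 (0.902 − 0.750). For model 1, R² = 0.15 gave a C-statistic of about 0.955, so its weaker-signal rows deserve attention.

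**4. Union over 20 imputed data sets as the pool.** Design: 20% missing in half of the predictors, 16 replicates, 8 bootstraps per imputed set. The 10-of-20 rule was applied at derivation but not inside the bootstrap.

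| Setting | Mean union size (of 40) | Slope: true / full / union |
|---|---|---|
| Model 2, R² 0.15, 8 true | 21.0 | 0.917 / 0.896 / 0.933 |
| Model 2, R² 0.15, 40 weak | 33.2 | 0.854 / 0.871 / 0.883 |
| Model 2, R² 0.05, 8 true | 18.1 | 0.803 / 0.808 / 0.882 |
| Model 1, R² 0.15, 8 true | 22.6 | 0.947 / 0.829 / 0.879 |

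The gap to the full pool narrows to between 0.012 and 0.074, always in the same direction. The standard error of the true slope is about 0.014 to 0.019.

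**5. Larger samples.** The article's figures suggest more than the minimum: 211,000 calls / 10 services × 0.90 aged 16 or over × 0.85 linkable ≈ 16,140 incidents. At 70% conveyed, that is about 11,300 conveyed and 4,840 not. Assuming 60% to 90% as many patients as incidents, models 1 and 3 have about 6,800 to 10,200 patients and model 2 about 2,900 to 4,360. With 10 true predictors, Nagelkerke R² 0.15 and a single data set (24 replicates × 8 bootstraps), slopes true / full / restricted were:
- Model 1: 0.94 / 0.90 / 0.96 at 6,800; 0.96 / 0.94 / 0.97 at 10,200
- Model 3: 0.98 / 0.96 / 0.98 at 6,800
- Model 2: 0.89 / 0.90 / 0.95 at 2,900; 0.94 / 0.93 / 0.97 at 4,360

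The gaps between pools are 0.02 to 0.06. With a weaker signal (R² not specified, so indicative only) the gap stayed near 0.10: 0.82 / 0.80 / 0.90 at n = 4,000 and 14% risk, and 0.83 / 0.79 / 0.90 at n = 10,000 and 4% risk.

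**The case against.** **Rejected candidates may return.** A reader might infer that a candidate dropped at derivation can never re-enter. The sentence can be read as the union over 20 imputed data sets. A candidate kept in 1 to 9 of them is then outside the final model but inside the bootstrap pool. This stands and reduces the effect (step 4). It helps only if imputation happens. The plan imputes only above 10% missingness, gives tests not clinically indicated their own category, and Table 3 reports under 2% missing for most core clinical variables, although wider items may have more. Without imputation the pool is survivors only, the worst case.

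**Too little shrinkage is not universal.** In the model 1 imputation run the true slope was 0.947, and the union pool at 0.879 already shrank too much. In a single-data-set run at n = 4,121 and 14% risk the slopes were 0.95 true, 0.91 full and 0.96 restricted, so the restricted pool was nearer the truth. This stands: the direction is firm against the promised process, not against the truth in every case.

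**The stated sizes are minima.** A reader might infer that about half of the needed shrinkage is lost. Some runs near the minimum sizes or with weak signal show that, but the runs at the likely sizes with stronger signal do not. The article gives neither the signal strength nor the final N, so it does not support a single fraction.

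**WP2 would show residual overfitting.** This stands in part. Temporal validation assesses calibration before WP3. But recalibration is tied to systematic under- or overprediction, and overfitting can leave the mean risk right and the slope wrong.

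**Conclusion.** The section contradicts itself on how the bootstrap selects predictors, and the two statements cannot both be followed. Under the closing sentence, estimated optimism is smaller and the shrinkage factor nearer 1 than under the full process; every simulation above agrees. Against true performance, the result is usually but not always too little shrinkage.

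The size is conditional on R², the number of true predictors, independent predictors, missingness and N, none of which the article settles. At the minimum sizes in a single data set, the factor was too high relative to the full process by 0.02 to 0.15. With the union pool the excess was 0.01 to 0.07. At the likely sizes with stronger signal it was 0.02 to 0.06. It would vanish only if the pool held every candidate. This should be fixed before derivation, but it does not by itself invalidate the models.

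**What to change.** Before derivation, delete the closing sentence or replace it with a rule to this effect: every bootstrap sample starts from the full pre-specified candidate list used at derivation, and repeats the choice of functional form, backward selection at p = 0.10 and the rule of at least 10 of 20 imputed data sets. To apply that last rule, resample the same patients across all 20 imputed data sets. If the sentence was meant for another step, name that step.

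The cost is computing time: 500 × 20 = 10,000 selections per model and outcome window when all 20 imputed data sets are used, each starting from 40 or more parameters rather than the survivors. Reported performance will be slightly less favourable. No new data are needed.
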